## 4. Methods

### 4.1. Design

We will implement a clustered randomized controlled trial with a parallel repeated-measures design. In the trial, 80 to 100 schools with 5th and 6th grade classes will be recruited across Quebec and be randomly assigned to one of the following conditions: 1) *Open Sky School* intervention (intervention group) and 2) teaching as usual (waitlist control group, who will receive the intervention the following school year if it is effective). We will randomize at the school level rather than at the class level to allow for more than one class within the same school to take part in the project while avoiding possible contamination effects. In the context of our project we define our nature intervention by exposing children to natural environments during school hours and including any activity that promotes learning or mental health. The available natural space must be located near the school, within a 1 kilometer radius, and can be, for instance, an urban park, wooded area or waterfront. In other words, we are interested in engaging children in nature (in urban or rural areas) and providing access to academic or mental health activities in order to promote their wellbeing.

### 4.2. Randomization

Randomization will occur after baseline assessments. Once randomization has occurred, it will not be possible to blind researchers and participants within our design. A simple computer algorithm will be used to randomly allocate schools to two parallel and balanced conditions (intervention or control; 1:1 while considering class sizes) by an independent researcher not involved in the study. This will ensure that all schools have an equal opportunity to be allocated into one of the two groups. In the event that multiple teachers from the same school consent to participate, they will be allocated to the same experimental condition to avoid contamination effects.

**Figure 1.** Flow chart of inclusion of participants.

[figure not shown]

Note. a 280 schools in 29 school boards were initially eligible. 4 school boards encompassing 32 schools did not agree to participate and were therefore removed from the recruitment process. b If more than 100 teachers consent to participate, we will randomly select 100 teachers to participate in the trial. c Parents and students must provide informed consent for students to participate in the assessments. Students who do not participate in assessments will still participate in the Open Sky School program. d In the event that multiple teachers from the same school consent to participate, they will be allocated to the same experimental condition to avoid contamination effects. If recruitment targets at the pre-selected school are not met, we will advertise online.

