## **8. Statistical analyses and power**

All analyses will be conducted at the cluster level, i.e., at the school level. Dependent variables will be measured on a continuous scale. Child mental health will be assessed at T1, T2, T3. A longitudinal ANCOVA, as described in Liu et al (2009), will be used to estimate the main and moderating effects described above. The characteristics of the intervention group and the control group will be compared at the class level, where means (e.g., socioeconomic deprivation) could be added to the model as covariates, in the unlikely event that randomization would not have balanced the two groups. A total of 80 to 100 schools (with a minimum of 40 classes if only one class per school participates) will detect small effects (power >90%). An intention-to-treat analysis approach will be used to increase the internal and external validity of the project. The analyses will include any child for whom at least one questionnaire has been completed at least one measurement time and the multiple imputations will be used in case of significant loss to follow-up.

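### When more than 100 teachers consent, the protocol draws teachers without regard to school; this gives up randomised schools for no saving in classes and can take their number below the planned 80 to 100

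*Protocol*

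**What the plan says.** The note to Figure 1 in Section 4.2 fixes what happens if the trial is oversubscribed: "If more than 100 teachers consent to participate, we will randomly select 100 teachers to participate in the trial". It does not stratify the draw by school or set a floor on the number of schools.

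The rest of the design is mostly counted in schools:

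- Section 4.1: "In the trial, 80 to 100 schools with 5 th and 6 th grade classes will be recruited across Quebec".
- Section 4.1, on the unit: "We will randomize at the school level rather than at the class level to allow for more than one class within the same school".
- Section 8, on analysis: "All analyses will be conducted at the cluster level, i.e., at the school level".
- Section 8 attaches power above 90% for small effects to "A total of 80 to 100 schools". A parenthesis there mentions a minimum of 40 classes.

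Several teachers per school are expected: "In the event that multiple teachers from the same school consent to participate, they will be allocated to the same experimental condition".

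The lay abstract gives the recruitment target as 80 to 100 classes, not schools.

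**The concern.** The cap limits the number of classes, which is reasonable as a limit on workload. It is applied by drawing teachers, though, while the precision of a school-randomised comparison depends mainly on the number of schools. Among 100 teachers drawn at random, some come from the same school, and some schools that volunteered a single teacher are lost altogether. The trial then runs the same 100 classes in fewer schools than it could have had. A trial that had recruited a number of schools within the planned range could end below that range because of its own selection rule.

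**Working it through.** **The plan's own figure.** The power statement (80 to 100 schools, over 90%) cannot be reproduced. Section 8 gives no effect size, significance level, intraclass correlation (ICC), children per class or pre-post correlation.

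**Schools kept by the draw.** Let T be the number of consenting teachers and draw 100 without replacement. A school with one consenting teacher is kept with probability 100/T. A school with two is kept with probability 1 − (T−100)(T−101)/[T(T−1)]. Summing over schools gives the exact expected number kept. The chance of fewer than 80 comes from 20,000 simulated draws per scenario. The number of schools and the teachers per school are assumptions; the documents give neither.

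Worked example, 50 schools with one teacher and 50 with two, T = 150:

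- one-teacher schools: 50 × 100/150 = 33.3
- two-teacher schools: 50 × [1 − (50 × 49)/(150 × 149)] = 50 × 0.890 = 44.5
- total: 77.9 schools

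| Schools volunteering | With two teachers | T | Mean schools kept | Chance of fewer than 80 |
|---|---|---|---|---|
| 100 | 0 | 100 | 100 (no draw) | 0 |
| 100 | 20 | 120 | 86.1 | about 0 |
| 100 | 30 | 130 | 82.3 | about 9% |
| 100 | 40 | 140 | 79.7 | about 47% |
| 100 | 50 | 150 | 77.9 | about 75% |
| 100 | 100 | 200 | 75.1 | about 96% |
| 80 | 40 | 120 | 72.3 | every simulated draw |
| 120 | 60 | 180 | 81.6 | about 21% |
| 150 | 75 | 225 | 85.3 | about 2% |

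**Cost in precision.** Let s, c and e be the school, class and residual shares of variance, m the children per class and S the schools holding the 100 classes. Relative to 100 schools with one class each, the variance of the effect is

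[s/S + (c + e/m)/100] ÷ [(s + c + e/m)/100].

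Assumed ranges: school ICC 0.02–0.10, class ICC 0.05–0.10, 12–18 children per class.

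- S = 78, mildest case (s = 0.02, c = 0.10, m = 12, e/m = 0.88/12 = 0.0733): 1 + 0.02 × (100/78 − 1)/0.1933 = 1.03.
- S = 78, strongest case (s = 0.10, c = 0.05, m = 18, e/m = 0.85/18 = 0.0472): 1 + 0.10 × (100/78 − 1)/0.1972 = 1.14.
- S = 70, same two cases: 1.04 and 1.22.

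The loss is therefore 3–14% with 78 schools and 4–22% with 70. The formula spreads the 100 classes evenly over the schools. In reality 78 schools would hold 56 single classes and 22 pairs. If classes are weighted equally, these act like 100²/(56 + 4 × 22) = 69 equal-sized schools, so the 78-school figure is somewhat optimistic.

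**Against the lower end of the plan.** Set against 80 schools with one class each, the same formula gives 0.8 times the ratios above: 0.82–0.91 with 78 schools and 0.84–0.97 with 70. On this formula, 100 classes in 70 to 78 schools are no less precise than 80 single-class schools.

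**Illustrative power.** Assume a standardised difference of 0.2, 20 children per class, school ICC 0.05, no separate class ICC, no gain from covariates and two-sided alpha 0.05. Power is 0.89 for 100 schools with one class, 0.84 for 75 schools holding 100 classes, and 0.82 for 80 schools with one class.

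**The case against.** **The cap has a textual basis.** The lay abstract sets the target at 80 to 100 classes, and a cap of 100 teachers fits that. This stands: the document is not uniformly in schools. It shows that the units need reconciling; it does not supply a reason to draw without regard to school.

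**Eighty is not a stated minimum.** A reader might infer that the rule breaches a floor. Sections 4.1 and 8 give a range, and the only figure called a minimum is 40 classes. This stands.

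**The stated power might be thought lost.** The documents do not support that. Their power claim cannot be recalculated, and the second classes largely make up for the lost schools when the comparison is with 80 single-class schools. How far depends on weighting: with unweighted school means and at most two classes per school, the variance relative to that benchmark is at most 0.95 with 78 schools and about 1.02 with 70.

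**It may never happen.** The rule applies only if more than 100 teachers consent, and the protocol also provides for under-recruitment by advertising online. The chance of fewer than 80 schools is near zero if only 20 of 100 schools have two teachers, and it fades when well over 120 schools volunteer. This limits how much the point matters.

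**A simple draw treats teachers equally.** Drawing by school lowers the selection chance of teachers in multi-teacher schools. That is a real cost, though small beside the gain in clusters.

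**Conclusion.** The point holds as a matter of efficiency. In an oversubscribed trial the written rule gives up schools for no saving in classes, and it can leave fewer than the 80 to 100 schools planned. Under the assumed recruitment patterns with 100 schools, the expected number kept reaches about 80 once 40 of them have two consenting teachers. If 80 schools volunteer with 120 teachers, about 72 remain. The precision cost against the best use of 100 classes is modest, at roughly 3–14% more variance with 78 schools and 4–22% with 70. All of this rests on assumed numbers of schools, teachers per school, ICCs and class sizes. No bias is claimed, and no failure of the stated power is demonstrated.

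**What to change.** Replace the sentence in the note to Figure 1. When more than 100 teachers consent, first take one randomly chosen teacher from every consenting school (drawing 100 schools at random if more than 100 consent), then add further teachers at random until 100 classes are reached. With 100 volunteering schools this keeps all 100; with 80 schools and 120 teachers it keeps all 80, with 20 second classes. State the recruitment target in one unit, or in both schools and classes, consistently across the lay abstract, Section 4.1, the note to Figure 1 and Section 8.

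The cost is a few sentences of text and a lower chance of selection for teachers in multi-teacher schools. The number of classes stays capped at 100.

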### 4.3. Measurement times

Children's mental health will be assessed by the teacher and self-reported by the child first before randomization (T1: March 2023), then after the intervention at the end of the school year (T2: June 2023) during class time. Since we anticipate the intervention's effects will be maintained in the medium term, children will fill out questionnaires again (self-reported mental health) (T3: September 2023), i.e. 3 months after the intervention ends. For T3, we will contact parents so that the children can fill in the questionnaires online. The clustered randomized controlled trial will be conducted without blinding participants to conditions, as it is not possible to implement a double-blind design with teachers and children.

### 4.4. Recruitment strategy and timeline

Participating schools will be recruited from a list of 280 French language elementary schools in the Canadian province of Quebec, enrolled in a larger study conducted by the Observatory for Children's Education and Health, which aims to document the consequences of the COVID-19 pandemic on 4th grade children's academic achievement ([www.observatoireenfants.ca/en](http://www.observatoireenfants.ca/en)). Eligible schools will receive an initial invitation letter by email (December 2022), containing a 90 second informative video, which they will be asked to distribute to their 5-6th grade teachers. In the invitation letter, 5-6th grade teachers will be invited to attend an online information session describing their involvement in the *Open Sky School* project. All interested teachers will be sent an information and consent form. Once teachers consent to take part in the study, they will distribute information and consent forms to students and students' parents. To maximize recruitment potential, we will also post a recruitment flyer via social networks inviting interested participants to contact us via email to receive the aforementioned information describing their involvement in the project.

Baseline assessment will take place from March 6 to 10, 2023 and post-test assessments will be conducted from June 5 to 12, 2023. The weekly 2-hour nature visits will take place from March 13, 2023 to June 2, 2023. The follow-up assessments will be administered from September 18 to 23, 2023. To encourage participation throughout the study, teachers will be compensated \$100 CAD for evaluating their students' mental health symptoms before and after the intervention (up to \$200 CAD total). Children can choose to participate in a draw to win gift cards to a local bookstore. More specifically, we will draw two \$50 CAD gift cards per class for children who complete questionnaires at baseline and immediate follow up, and ten \$100 CAD gift cards for children who complete the follow-up assessment. Figure 1 shows a flow chart of the inclusion of participants.

### 4.5. Data collection, analysis and dissemination

Data will be collected online using Qualtrics, a widely used software in analytics and research. Confidential data (e.g., name, zip code) will be uploaded to a private and secure computer and then periodically erased from the server. The data file to be analyzed will contain only the anonymous (numeric) identifier and the questionnaire responses. The file linking the identifiers to the data file will be kept on an encrypted USB key, protected by a password and kept in a locked safe. The safe will be kept in [name] and research coordinator's work office. Only [name] and the coordinator will have access to it. When data collection is complete, the data will be downloaded to a private computer and then deleted from Qualtrics. Members of the research team responsible for analyzing data will only have access to this anonymous dataset which will be used solely for the purpose of establishing and disseminating research findings. Results will be disseminated to researchers, stakeholders, policy-makers and participants via scientific publications, oral presentations, interviews, and

outreach. All communications related to the project will be made available publicly on the official website <https://www.ecolecielouvert.ca/>.

## **5. Instruments for measuring primary and secondary outcome measures**

| Measures                                                 | Measure                                                       | Participant        | T1 | T2 | T3 |
|----------------------------------------------------------|---------------------------------------------------------------|--------------------|----|----|----|
| Sociodemographics                                 |                                                               | Student            | •  |    | •  |
| For children                                      |                                                               |                    |    |    |    |
| Mental health                                     |                                                               |                    |    |    |    |
| General mental health                             | Social Behaviour Questionnaire                                | Student            | •  | •  | •  |
| General mental health                             | Social Behaviour Questionnaire                                | Teacher            | •  | •  | •  |
| Depressive symptoms                               | Children's Depression Inventory-Short Version                 | Student            | •  | •  | •  |
| Positive and negative affect                      | Positive and Negative Affect Schedule-Child                   | Student            | •  | •  | •  |
| Relationship with the environment                 |                                                               |                    |    |    |    |
| Connection with nature                            | Nature Connection Index (NCI)                                 | Student            | •  | •  | •  |
| Pro-environmental behaviours                      | Taken from Keith et al.                                       | Student            | •  | •  | •  |
| Program evaluation                                |                                                               |                    |    |    |    |
| Appreciation of the program                       | Ad hoc                                                        | Student            |    | •  |    |
| For teachers                                      |                                                               |                    |    |    |    |
| Wellbeing                                         | World Health Organization Wellbeing Index (WHO-5)             | Teacher            | •  | •  |    |
| Teachers' enjoyment of teaching outdoors          | Enjoyment of Teaching Mathematics Scale - adapted             | Teacher            |    | •  |    |
| Positive and negative affect                      | Positive and Negative Affect Schedule                         | Teacher            | •  | •  |    |
| Moderators                                        |                                                               |                    |    |    |    |
| Qualifications and experience of teachers         | Ad hoc                                                        | Teacher            | •  |    |    |
| Teachers' prior experience with outdoor education | Taken from Ayotte-Beaudet et al.                              | Teacher            | •  |    |    |
| Neighbourhood greenness                           | Normalized Difference Vegetation Index                        | CANUE a | •  |    |    |
| Child disability status                           | Diagnoses of disability, adjustment and learning disabilities | Teacher            | •  |    |    |
| Sex                                               | Male, female                                                  | Student            | •  |    |    |
| School Socioeconomic status                       | Ministry of Education                                         | MEQ b   | •  |    |    |

a. CANUE: Canadian Urban Environmental Health Research Consortium

b. MEQ: Ministère de l'Éducation du Québec / Québec Ministry of Education

### **5.1. Primary outcome: Mental health symptoms**

The Social Behavior Questionnaire is a 30 item questionnaire that will be used to assess a range of mental health symptoms in children. The instrument incorporates items adapted from the Child Behavior Checklist, the Ontario Child Health Study Scales and the Preschool Behavior Questionnaire used in the Quebec Longitudinal Study of Child Development. The frequency of

children's symptoms over the last 2 months is rated on a 3-point scale (never/not true = 0, sometimes/somewhat true = 1, often/very true = 2). Overall symptoms will be examined as outcomes, as well as internalizing symptoms (emotional distress and withdrawal; 11 items), externalizing symptoms (impulsive/hyperactive/inattentive and disruptive behaviors; 13 items), and social behaviors (pro-social behavior and peer relationships; 6 items). Ratings will be obtained by both child and teacher reports which will be analyzed separately.

## 5.2. Secondary outcomes

*Additional mental health indicators for children.* The Positive and Negative Affect Schedule for Child (PANAS-C) is a 20-item scale that will be used to assess positive (e.g., "excited") and negative (e.g., "upset") affect which has good convergent and discriminate validity among children. Children will indicate to what extent they experience feelings over the last 2 weeks (1 = very slightly or not at all; 5 = extremely). The Children's Depression Inventory-Short Version (CDI-S) includes 13 items that will be used to assess cognitive, affective and behavioral signs of depression in children. The CDI-S has good convergent, discriminate and factorial validity among children. Children consider how they were feeling over the last 2 weeks and respond on a 3-point scale (e.g. 1 = I hate myself; 2 = I don't like myself; 3 = I like myself).

*Connection with nature for children.* The Nature Connection Index (NCI) is a self-report questionnaire including 6 items that will be used to assess connectedness to nature. The scale has good validity and reliability among children. Participants respond to affirmations (e.g., nature always makes me happy) using a 7-point scale (1 = strongly agree; 7 = strongly disagree).

*Pro-environmental behaviors* will be measured by a brief 6-item questionnaire developed in a recent study, that asks children to report the frequency they made an effort to conserve water, energy and recycle trash (1 = always; 5 = never) and the extent to which they agree that they are ready to volunteer, give money and talk to their entourage to protect nature (1 = strongly agree; 4 = strongly disagree). Additionally children will be asked about their pro-environmental behaviors in the context of climate change using 4 self-report questions, adapted from a previous study and refined by experts. Children report the extent to which they are worried about climate change (1 = not at all worried; 4 = extremely worried), that these worries motivate them to engage in pro-environmental behaviors or activism (1 = not at all; 4 = a lot) and that they feel capable of making behavioral changes to help the environment (1 = strongly disagree; 4 = strongly agree).

*Well-being for teachers.* The World Health Organization Well-Being Index (WHO-5) is a 5-item self-report measure that will assess of wellbeing for adults. The WHO-5 is a widely used, valid and reliable measure that is sensitive to change. Participants indicate the frequency of their feelings (e.g. in a good mood) over the last two weeks (5 = all the time; 0 = never). The Positive and Negative Affect Schedule (PANAS) is a 20-item self-report measure that will be used to assess positive (e.g., "excited") and negative (e.g., "upset") affect which has well-established good psychometric properties. Teachers will indicate to what extent they experience feelings over the last two weeks (1 = very slightly or not at all; 5 = extremely).

*Appreciation of outdoor activities for children and teachers.* An adapted version of the Enjoyment of Teaching Mathematics Scale will be used for teachers from the intervention group at post-test to self-report their enjoyment of teaching outdoors (e.g. I really like teaching outdoors) with 5 items on a 5 point scale (1 = strongly agree; 5 = strongly disagree). We designed one item for children to self-report the frequency that they appreciated the intervention (1 = not at all; 4 = always) that will be administered in the intervention group at post-test.

